#### SDMs

RA’s will assist patients with identifying a SDM using a pre-written script which asks whether the patient has formally appointed someone, and if not, who may be able or willing to fulfill this role. If the SDM is present at the time of the visit, they will be asked if they would like to participate. If the SDM is not present, the researchers will ask permission from the patient to contact them regarding the study. If such a person wishes to participate, they will also be asked to provide informed consent.

### Assignment of interventions

#### Allocation

Randomization will be performed at the level of the GP to avoid contamination bias. Every GP will have to recruit at least three patients. Once three patients have been recruited, the GP will be randomized to either the intervention or control group according to a 1:1 allocation ratio per a computer-generated randomization list. We will use permuted block randomization with varying block sizes. No stratification factors will be taken into account.

Participants will be enrolled to the study by the research assistants and data managers. The allocation sequence will be generated by independent statisticians working with the Biostatistics Unit at the Faculty of Medicine and Health Sciences of Ghent University. Assignment to intervention or control groups of GP-patient clusters will be performed by a researcher not involved with any other portion of this study.

#### Blinding

Due to the nature of the intervention, neither GP, patient, nor SDM participants can be blinded to allocation. Although the participants cannot be blinded to their assignment and researchers will be unblinded to GP assignment through the coordination of the training sessions, data collection at T0, T1, and T2 will be performed by an independent data collector/research assistant who is blinded to the assignment of the GP and patient to either the intervention or control arm. Those performing the data analysis will likewise remain blind to participant allocation.

Informed consent and data collection at T0 will occur before randomization has taken place.

### Data collection, management, and analysis

#### Data collection methods

The outcome measures and general procedures for data collection are described above. Questionnaire data will be collected at T0, T1, and T2. GPs have the option to complete the questionnaires on paper or online if preferred. Patients and SDMs will complete questionnaires on paper. Patients and SDMs completing the questionnaires at T0 and T1 can receive support from a data manager if so desired, either through an in-person visit by the data manager or via telephone contact. If COVID-19 safety concerns arise which prohibit home visits, all support will be provided through telephone contact.

As described above, data collection for the process evaluation will occur during and after the intervention period by means of questionnaires, documentation of activities, and audio-recordings of ACP conversations. These audio-recordings will be transcribed for analysis. During the recruitment phase, those approached for recruitment who do not wish to participate may optionally provide their reason for not participating.

After the 6-month intervention period has elapsed, the process evaluation will be continued through interviews and focus groups with patients and their SDMs, and GPs respectively. With permission from the participants, focus groups and interviews will be audiotaped to allow for later verbatim transcription. The interviewer will also take notes during the interviews and focus groups. Both the interviews and the focus groups will be conducted according to a topic list, with attached instructions for the interviewer (or moderator and observer for focus groups).

With patients in the intervention group and their SDM, if one was identified, 10–15 interviews will be conducted. Focus groups with GPs will include 6–8 GPs per focus group. Interviews and focus groups will be conducted until data saturation is achieved; that is, until the newly-collected data is redundant with the already-collected data and no new results emerge.

To improve retention, participants will be presented with a gift certificate for their participation in the study. Additionally, the consultation costs for the first two ACP discussions planned in the intervention group (i.e., the consultations required for the intervention) will be compensated by the researchers.

#### Data management

To pseudonymize the data, each participant will be assigned a study identification number. A list with identification codes which links the participant’s name to the participant’s identification number will be stored in a limited-access space. Response input will only use the participant identification number. All digitally inputted data will be stored on a secure server. Access to this server is strictly limited to those who require access to conduct the study. All informed consent forms will be stored in a lockable filing cabinet restricted to members of the research team. Paper questionnaires will be stored in a separate lockable filing cabinet with similar restrictions.

Data will be retained for 10 years, after which it will be destroyed. Data will be shared only for the purposes of the study and will not be shared with other countries.

A trial manager will take responsibility for the data management over the course of the study. A record of the study and its data processing activities has been submitted to the Data Protection Office (DPO) of the Vrije Universiteit Brussel.

#### Data analysis

The intent-to-treat population consists of all patients randomized. Subjects are analyzed according to the allocated treatment group irrespective of their compliance with the planned course of treatment. The intent-to-treat population is considered the main analysis population.

Linear mixed models will give unbiased results when outcome data is missing at random (maximum likelihood estimation). GEE models only allow for missing values to be completely at random (it is not a likelihood approach).

The analyses of the two separate primary endpoints will be performed at the two-sided 2.5% significance level, because success on any one of these endpoints at T1 may support a conclusion of effectiveness (Bonferroni method to adjust for multiplicity).

When an effect on a primary endpoint is shown, the secondary endpoints can be analyzed at the two-sided 5% significance level.

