**Methods:**

This RCT will take place in Flanders, Belgium. Thirty-six GPs, 108 patients with a chronic, life-limiting illness, and their (potential) SDM will be recruited, then cluster-randomized to the ACP-GP intervention or the control condition. The primary outcome for GPs is ACP self-efficacy; primary outcome for patients is level of ACP engagement. Secondary outcomes for GPs are ACP practices, knowledge and attitudes; and documentation of ACP discussion outcomes. Secondary outcomes for patients are quality of life; anxiety; depression; appointment of an SDM; completion of new ACP documents; thinking about ACP; and communication with the GP. The secondary outcome for the SDM is level of engagement with ACP. A process evaluation will assess the recruitment and implementation of the intervention using the RE-AIM framework.

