**Efficacy/effectiveness**	• Primary and secondary outcomes of the RCT	• See primary and secondary outcomes above • Reports of any adverse effects			
**Adoption**	• ACP discussion documents uploaded • Patient use of the work booklet • Experiences of GPs and patients applying intervention steps • Changes in GP practice	• Training topic checklist (after each training) • Questionnaire for GPs regarding their ACP practices and conversations in the last 3 months (T1) • Questionnaire for patients regarding ACP conversations with their GP in the last 3 months (T1) • Documentation template review (T1, T2) • Contents of work booklet from a sample of patients in the intervention group (physical copy or digital scan) (T1, T2) • Check-in discussions between GPs and trainers (continuous) • Focus groups with GPs (after T2) • Semi-structured interviews with patients and SDM (after T2)			
**Implementation**	• Fidelity: the extent to which the steps of the intervention were followed as specified in the protocol • Patient and GP barriers/facilitators to following the steps of the intervention • Satisfaction of GPs and patients with the intervention components	• Training topic checklist (after each training) • Check-in discussions between GP and trainers (continuous) • Audio recordings of ACP consultations between GP and patient (and SDM if present) • Documentation template review (T1, T2) • Satisfaction questionnaire for intervention GPs and patients (T1) • Focus groups with GPs (after T2) • Semi-structured interviews with patients and SDM (after T2)			
**Maintenance**	• GP intention for using the intervention materials in the future • Recommendations by the GP and patients to improve intervention usability in the future	• Satisfaction questionnaires for intervention GPs and patients (T1) • Focus groups with GPs (after T2) • Semi-structured interviews with patients and SDM (after T2)			

We have two separate primary outcomes, one at the GP level and one at the patient level. Success on any one of these outcomes at T1 may support a conclusion of effectiveness. Hence there are several ways for the study to successfully demonstrate a treatment effect. This multiplicity problem has been taken into account in the power analysis by controlling the Type I error rate at 2.5% (Bonferroni method).

Scores on the ACP Engagement Survey and the ACP Self-Efficacy Scale for GPs will also be measured at T2. We will treat T2 scores on these scales as a secondary outcome.

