#### Harms

The ACP intervention is a non-invasive intervention, focused on conversations between GPs, patients, and SDMs regarding values and wishes for future medical care. Previous research has shown that people with life-limiting illnesses see participating in research such as this study as a worthwhile endeavor [17]. Adverse effect from participating in similar research, as may be implied by dropout due to the subject being too psychologically taxing to talk about, are rare [33]. However, people living with chronic life-limiting illnesses are a vulnerable group for whom the appropriate concern and ethical measures must be in place. An anticipated adverse event which may arise during the intervention is mild psychological discomfort in participating patients and SDMs, which may be caused by some questions in the ACP Engagement Survey or the workbook, or as a result of ACP conversations with the GP. However, participants will be informed of their right to refuse to answer any question and that they may withdraw from the study at any time without negative consequence. The possibility of a patient or SDM becoming distressed during the ACP discussions will be discussed during the GP training.

As the study involves patients with a chronic, life-limiting illness, it is possible that some patient drop-out is due to death related to disease progression, but this would not be related to the study protocol. A bereavement protocol has been established for the SDM if the patient dies during the study period. If researchers are informed that a patient has died, this will be communicated to the ethics committee. The bereaved SDM will be contacted with condolences and, if necessary, will receive information to refer them to appropriate support resources.

While the investigators cannot predict the occurrence of unanticipated or unexpected adverse events, we do not anticipate any serious adverse events associated with the research protocol. Nevertheless, we have included measures to detect increases in anxiety and depression at T1 and T2 and will act accordingly in the case of adverse events. These will be reported to the principal investigator and forwarded to the ethics committee. In the case of an adverse event involving a patient, the GP and specialist health provider to the patient will be notified if necessary.

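### One primary success at 2.5% opens all secondary endpoints at an undivided 5%: more alpha than was earned, and at odds with their exploratory status

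*Protocol article*

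**What the plan says.** Two primary endpoints are assessed at T1: patient ACP engagement and GP self-efficacy. Under Study endpoints and assessments, either is enough: "Success on any one of these outcomes at T1 may support a conclusion of effectiveness". The Data analysis section sets the level: "The analyses of the two separate primary endpoints will be performed at the two-sided 2.5% significance level". It names Bonferroni as the method.

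The next rule in that section is the one at issue: "When an effect on a primary endpoint is shown, the secondary endpoints can be analyzed at the two-sided 5% significance level". It gives no order among the secondaries, no division of the 5%, no lower level when only one primary succeeds, and no exemption for any endpoint.

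Three other places bear on it:

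- **Objectives.** The table reserves the verb *test* for the two primaries and *explore* for every secondary outcome.
- **Secondary efficacy analyses.** Mixed models for continuous secondaries and GEE models for the others are specified with no condition on the primary result.
- **Harms.** The protocol says "we have included measures to detect increases in anxiety and depression at T1 and T2". In Table 3 these measures are GAD-7 and PHQ-9, both listed as secondary outcomes.

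**The concern.** A Bonferroni split protects a total of 5% by giving each primary 2.5%. When one primary succeeds, its 2.5% may be passed on. The other 2.5% is still committed to the primary that has not succeeded. The rule passes on 5% rather than 2.5%, and gives it in full to every secondary instead of once to the family. A success on GP self-efficacy alone would open all patient and SDM endpoints.

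Making secondary tests wait for a primary success is the form of a confirmatory gatekeeping procedure. Exploratory analyses need no gate, and confirmatory ones need a gate that holds its level. A reader who sees p<0.05 on a secondary after a passed gate may take it as protected.

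The same sentence covers GAD-7 and PHQ-9. If neither primary is positive, it licenses no significance test of whether anxiety or depression rose in the intervention arm. Yet an intervention with no benefit and some added distress is a case in which that comparison is wanted.

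**Working it through.** **Inputs.** The two-sided level is 2.5% for each of two primaries (Data analysis). Planned power is 91.45% for the patient primary: 26 per group, difference 1, SD 0.96, design effect 1.04. It is 91.11% for the GP primary: 14 per group, difference 1, SD 0.71 (Sample size).

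**Reproducing the plan's figures.** The patient SD with the design effect is 0.96 × √1.04 = 0.979.

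| Primary | Stated power | Noncentral t, 2.5% | Normal approximation, 2.5% | Noncentral t, 5% |
|---|---|---|---|---|
| Patient | 91.45% | 91.1% | 92.5% | 95.1% |
| GP | 91.11% | 90.4% | 93.1% | 94.8% |

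The stated powers lie between the two methods at 2.5%, so the calculation does use the split level. The split sums to 2.5% + 2.5% = 5%.

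**Counting the secondaries.** The abstract names seven for patients (six in "Secondary outcomes for patients are quality of life; anxiety; depression; appointment of an SDM; completion of new ACP documents; thinking about ACP", plus a seventh on how patients and GPs communicate), four for GPs ("Secondary outcomes for GPs are ACP practices, knowledge and attitudes; and documentation of ACP discussion outcomes") and one for SDMs ("The secondary outcome for the SDM is level of engagement with ACP"): 7 + 4 + 1 = 12. Adding the two primary scales at T2, which the protocol makes secondary, gives 14. Counting the SF-12 physical and mental scores separately (+1) and the three SDM domain scores separately (+2) gives 17. Separate T1 and T2 tests would add more.

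**If nothing works.** A secondary claim needs an open gate, and the gate opens with probability 1 − 0.975² = 4.9% if the primaries are independent, and never more than 5%. Family-wise error is held here.

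**If one primary works, the other is null, and k secondaries are null and independent.** No error occurs when the null primary is not significant and either the gate stays shut or no secondary is significant:

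FWER = 1 − 0.975 × (0.9145 × 0.95^k + 0.0855)

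- k = 1: 1 − 0.975 × (0.8688 + 0.0855) = 7.0%
- k = 12: 1 − 0.975 × (0.4942 + 0.0855) = 43.5%

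The excess is there with one secondary, before the number of endpoints matters. With 12, the chance of a false positive among the secondaries alone, once the gate is open, is 1 − 0.95^12 = 46.0%.

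**With correlation.** The protocol gives no correlations, so a common pairwise value across all test statistics, primaries included, was assumed and simulated (400,000 draws for k = 1, 100,000 otherwise):

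| Correlation | k = 1 | k = 12 | k = 14 | k = 17 |
|---|---|---|---|---|
| 0 | 7.0% | 43.4% | 48.1% | 54.4% |
| 0.3 | 6.7% | 36.5% | 40.4% | 45.2% |
| 0.5 | 6.1% | 28.2% | 30.9% | 34.3% |
| 0.8 | 4.8% | 14.1% | 15.0% | 16.3% |

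With 12 or more secondaries the rate is well above 5% throughout. Only the single-secondary case at 0.8 falls below it.

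**If only the earned alpha is passed on.** After one success, 12 secondaries share 2.5%: 0.025/12 = 0.0021 each. They share 5% only if both primaries succeed. The simulated rate is then 4.7% (independent) to 2.7% (correlation 0.8). Testing each secondary at 2.5% without sharing is not enough: 25.9% for 12 independent ones.

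**The gate and the harm measures.** With both primaries null and independent, the gate stays shut with probability 0.975² = 95.1%. In those trials the Data analysis section offers no significance test of GAD-7 or PHQ-9, while Secondary efficacy analyses still has their models fitted.

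**The case against.** The strongest reply is that the protocol makes no confirmatory claim for secondaries. The Objectives only explore them, effectiveness rests on the primaries at T1, and a nominal 5% for exploratory outcomes is conventional. That limits the weight of the point but does not remove it. The gate is written into the document and is not something left to an analysis plan, and it contradicts that exploratory status.

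Four stronger readings are tempting and are not supported:

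- *That anxiety and depression are analysed only if efficacy is shown.* Secondary efficacy analyses fits the models for continuous endpoints unconditionally, which covers the GAD-7 and PHQ-9 sum scores. The monitoring and reporting of adverse events under Harms does not depend on efficacy. The gate sentence can even be read as setting only the test level. What remains is the formal between-arm test, on which the two sections need reconciling.
- *That the gate gives no error control.* It holds family-wise error at 5% or below when nothing works. It fails once one primary is truly effective.
- *That a false secondary claim is about an even bet.* Rates near 50% need independence and every secondary null beside a working primary. Several secondaries, such as GP knowledge and documentation, are direct targets of the intervention, so a complete null is a worst case, and correlation lowers the figure.
- *That Bonferroni for the primaries is a mistake.* It is valid and matches the level used for the sample size.

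**Conclusion.** The point holds as an error in a stated rule. One success at 2.5% releases 2.5% to be shared, and the protocol releases 5% to each secondary. With one primary effective at the planned power and the other null, family-wise error is about 7% for one independent null secondary. For the 12 named secondaries, all null, it is about 43% (independent), 28% (correlation 0.5) or 14% (correlation 0.8). The count comes from the protocol's lists. The correlations and the all-null setting are assumptions.

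The gate also contradicts the Objectives and Secondary efficacy analyses. On harm the gap is narrow: read literally, there is no between-arm significance test of GAD-7 or PHQ-9 when neither primary is positive. The primary analyses and their levels are unaffected.

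**What to change.** Replace the gate sentence in Data analysis with two statements:

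1. All secondary endpoints are analysed and reported whatever the primary result, as estimates with 95% confidence intervals labelled exploratory, with no confirmatory claim.
2. GAD-7 and PHQ-9 are always compared by arm at T1 and T2.

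This brings the section into line with the Objectives, Secondary efficacy analyses and Harms. If confirmatory secondary claims are wanted, pass on only the alpha earned (2.5% after one primary success, 5% after both), shared across the secondaries.

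The cost is wording: the sponsor gives up confirmatory language for secondaries. Sample size and data collection do not change. The change should be made before any unblinded analysis, so that it cannot appear driven by results.

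Optional, and not the correction of an error: Holm for the two primaries (smaller p-value at 2.5%, then the other at 5%) keeps 5% control. It raises power for the second primary, once the first is significant, from about 91% to about 95%.

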##### Descriptive statistics

Demographic characteristics of participants (at T0) will be summarized using descriptive statistics (absolute and relative frequencies for nominal variables, mean and standard deviation for continuous variables with normal distribution, median and 25-75th percentiles for continuous variables without normal distribution).

##### Primary efficacy analyses

To test the effectiveness of the intervention, we will compare T1 scores on the ACP Engagement Survey for patients and the ACP-Self Efficacy Scale for GPs between the intervention and control arms. Linear mixed models will be used. For patient outcomes, the models will include a random intercept for GP (to account for the nesting of patients within a GP) and a random intercept for patient (to account for the nesting of repeated measurements within a patient). For GP outcomes, a random intercept for GP (to account for the nesting of repeated measurements within a GP) will be used. The fixed effects part of these linear mixed models will include time, group, and time x group interaction. The two-way interaction between time and group will capture the effect of the intervention.

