### Outcomes

#### Study endpoints and assessments

This study uses both qualitative and quantitative data to measure the outcomes of the intervention. As the intervention consists of components developed for the GP and patient, outcomes will be measured at both levels. The primary and secondary outcomes are listed in Table 3.

**Table 3 Tab3:** Outcomes, measurement instruments and timing

	Measurement tool	Completed by	Timing of measurement		
Primary outcome			T0	T1	T2
Level of engagement with ACP	*ACP Engagement Survey 15-item version* [24] • Reported on an overall average 5-point Likert scale (range 1–5)	Patient	X	**X**	X
ACP Self-efficacy	*ACP Self-efficacy Scale (ACP-SE)* [25] • 17 items • Reported on an overall average 5-point Likert scale (range 1–5) • 1 additional general item including all advance care planning can be used for comparison to the scale	GP	X	**X**	X
Secondary outcomes					
Health-related quality of life	*Short Form Health Questionnaire (SF-12v2)* [26] • Physical Health (PCS) and Mental Health (MCS) summary scores (range 0–100)	Patient	X	X	X
Anxiety	*Generalized Anxiety Disorder Questionnaire (GAD-7)* [27] • Sum score (range 0–21)	Patient	X	X	X
Depression	*Patient Health Questionnaire (PHQ-9)* [28] • Sum score (range 0–27)	Patient	X	X	X
Appointment of a substitute decision maker	GP report ACP engagement survey “readiness to sign official papers assigning a SDM” item	Patient GP	X	X	X
Completion of new ACP documents	Patient report GP report ACP engagement survey “readiness to sign official papers stating medical wishes” item	Patient		X	X
Thinking about ACP	1 self-developed item, 10-point Likert (“How much have you thought about ACP in the last 3 months?”; response categories range from “not at all” to “very much”)	Patient	X	X	X
Communication with the GP	4 self-developed items, 10-point Likert (e.g., “To what extent did the GP listen to your concerns about your future health?”; response categories range from “not at all” to “very much”)	Patient	X	X	X

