ACP Practices	• *Next Steps training program questionnaire* [29] (4 items) • 2 items specific to practices with patients with chronic, life-limiting illness (“Which percentage of your patients has a chronic, life-limiting illness” and “With which percentage of your patients with a chronic, life-limiting illness do you conduct ACP conversations?”; 4 response options per item) [25] • 8 additional items regarding ACP practices (e.g., “Where do the ACP conversations you conduct usually take place?”)	GP	X	X	X
ACP Attitudes	*Next Steps training program questionnaire* [29] • 9 items; 5-point Likert scale ranging from “Completely disagree” to “Completely agree”; adapted to the Belgian legal context	GP	X	X	X
ACP Knowledge	*Next Steps training program questionnaire* [29, 30] • 10 items; correct/not correct/don’t know; adapted to the Belgian legal context	GP	X	X	X
Documentation of ACP discussion outcomes	Documentation template review	GP		X	X
Level of engagement with ACP	*ACP Engagement Survey, substitute decision maker version* [31] • 17 items; 5-point Likert scales • 3 domain scores (“Serving as SDM”, “Contemplation”, Readiness”) computed as the unweighted average of items per domain (range 1–5)	SDM	X	X	X
Other measurements					
Demographic information	For patients and surrogate decision makers: • Gender • Age • Marital status • Highest completed education • Religion • Patient/SDM relationship • Whether patient and SDM live together or apart For patients: • Previous completion of any advance directives (“wilsverklaringen”) For surrogate decision makers: • How long they have known the patient For GPs: • Gender • Age • Graduation year • Practice setting(s) • Years of experience as a GP • Graduating university • Working in a palliative home care team (yes/no) • Working as a “coordinating and advising practitioner” in a residential care facility (yes/no) • Prior formal ACP education or training (intensive/introductory/none) • Prior formal palliative care education or training (intensive/introductory/none)	GP Patient SDM	X		
Process evaluation					
**RE-AIM domain**	**Operationalization**	**Measurement**			
**Reach**	• Comparing the characteristics of participating patients with non-participants	• Documentation of the recruitment process by the researchers • Documentation of reasons given for not participating • Participant demographics			

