##### Secondary efficacy analyses

All continuous secondary endpoints will be analyzed by fitting similar linear mixed models as described above. Binary, multinomial, ordinal and count endpoints will be analyzed by fitting Generalizing Estimating Equations (GEE) models using a compound symmetry (or exchangeable) correlation structure, where we assume all correlations between time points to be the same. The GEE approach is a robust approach to take into account the repeated measurements within GPs without distributional assumptions. It is robust against misspecification of the covariance structure. However, it only allows missing values to be missing completely at random. Only an independent correlation structure is available for multinomial GEE models in SAS and SPPS software. Therefore, for nominal endpoints with K response categories, we will fit K-1 separate binary logistic GEE models for each response category paired with a baseline category.

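### Completion of new ACP documents has no T0 measurement, and the only model effect parameter the article names, time by group, would not estimate the intervention effect if carried over to it

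*Protocol article*

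**What the plan says.** In the Protocol article, *Primary efficacy analyses* opens with the comparison of interest: "we will compare T1 scores on the ACP Engagement Survey for patients and the ACP-Self Efficacy Scale for GPs between the intervention and control arms". It then sets out linear mixed models whose fixed part "will include time, group, and time x group interaction", and concludes that "The two-way interaction between time and group will capture the effect of the intervention". Both primary outcomes are marked at T0, T1 and T2 in Table 3.

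*Secondary efficacy analyses* treats the remaining endpoints in two groups:

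- Continuous endpoints follow the primary approach: "All continuous secondary endpoints will be analyzed by fitting similar linear mixed models as described above".
- The other endpoint types get a different method: "Binary, multinomial, ordinal and count endpoints will be analyzed by fitting Generalizing Estimating Equations (GEE) models", with an exchangeable correlation structure. The section justifies this choice ("The GEE approach is a robust approach to take into account the repeated measurements within GPs without distributional assumptions") and covers missing data and nominal outcomes. It gives no fixed effects and no effect parameter for the GEE models.

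Table 3 (*Study endpoints and assessments*) lists "Completion of new ACP documents" as a patient-level secondary outcome with the T0 column blank and marks at T1 and T2. The GP-level endpoint on documenting ACP discussions, measured by "Documentation template review", has the same schedule. The *Objectives* table places both among the outcomes whose effects are to be explored. Table 3 also records, at baseline, whether the patient had completed any advance directive before.

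**The concern.** A time-by-group term measures an intervention effect when the reference time point comes before the intervention. T0 does: the *Blinding* section places it before randomisation. T1 and T2 do not. For an endpoint seen only at T1 and T2, the interaction asks whether the arm difference grew or shrank between two post-randomisation visits. The intervention effect itself sits in the arm contrast at each visit.

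Time by group is the only model effect parameter the article names, and no exception is stated for endpoints without a baseline value. An analyst who extended it by default to completion of new documents would be testing the wrong quantity. An early gain that is then maintained would give an interaction near zero. A real T1 benefit followed by later catch-up among controls would give an interaction pointing the wrong way.

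An early gain is a plausible success pattern. Table 2 places the first ACP conversation within 2 weeks of the GP's training and the second within a month of the first, while T1 is at 3 months. The article does not fix the interval from T0 to the training, so this is plausible rather than certain.

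**Working it through.** **The plan's own figures.** The article gives no expected rate or power for document completion. Its power figures concern the primary outcomes and reproduce to about one percentage point (noncentral t, two-sided alpha 0.025). For patients, the effective n is 26/1.04 = 25 per arm, difference 1, SD 0.96: 91.1% against the stated 91.45%. For GPs, n = 14 per arm, difference 1, SD 0.71: 90.3% against the stated 91.11%. Neither is affected by this point.

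**Algebra.** Take the mean model on the link scale, with T1 as reference because there is no T0:

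link(mean) = b0 + b1·group + b2·[T2] + b3·group·[T2]

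- Arm contrast at T1 = b1
- Arm contrast at T2 = b1 + b3
- Time by group: b3 = (T2 contrast) − (T1 contrast)

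If the arm contrast is the same at both visits, b3 = 0 whatever the size of b1. For a primary outcome with T0 as reference, the group-by-T1 term is the T1 contrast minus the T0 contrast. Randomisation makes the T0 contrast zero in expectation, so there the interaction is the intervention effect.

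**Illustrations (all completion rates assumed).**

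1. Sustained effect, 40% v 10% at T1 and 45% v 12% at T2.
   - T1 odds ratio = (0.40/0.60)/(0.10/0.90) = 6.0
   - T2 odds ratio = (0.45/0.55)/(0.12/0.88) = 6.0
   - Interaction odds ratio = 6.0/6.0 = 1.0
2. Late catch-up by controls, 40% v 10% at T1 and 40% v 25% at T2.
   - T1 odds ratio = 6.0
   - T2 odds ratio = (0.40/0.60)/(0.25/0.75) = 2.0
   - Interaction odds ratio = 2.0/6.0 = 0.33, although the intervention arm is ahead at both visits

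**Simulation.** Logistic GEE with an exchangeable structure clustered by GP, 14 GPs with 2 patients each per arm (14 × 2 = 28 patients), T1 and T2 only, two-sided 5% level, 500 data sets per scenario. Outcomes were correlated within patient across visits. No correlation between patients of the same GP was generated.

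| Assumed control/intervention at T1, then T2 | True T1 log OR | True interaction log OR | Interaction test rejects | T1 contrast rejects |
|---|---|---|---|---|
| 15%/55%, then 15%/55% | 1.94 | 0 | 5.2% | 89.2% |
| 15%/55%, then 20%/60% | 1.94 | −0.14 | 5.8% | 86.6% |
| 15%/35%, then 15%/55% | 1.12 | 0.82 | 26.2% | 42.4% |

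In the first two scenarios the interaction test rejects at about its nominal level, while the T1 contrast from the same fitted model usually detects the effect. Even where the effect grows between visits, the T1 contrast rejects more often.

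**The case against.** The strongest reply is that the article never says time by group will be used for this endpoint. The quoted sentence belongs to the primary linear mixed models and is correct there. The explicit extension to similar models covers continuous secondary endpoints only. Completion of documents is most naturally binary or a count, so it falls under GEE, for which no mean model is stated. This stands: the carry-over is an inference, and the contrast may be named in a full protocol or SAP that is not shown.

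Three further points also stand, in whole or in part.

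- *Primary efficacy analyses* declares a between-arm comparison at T1, which is close to the remedy. It is written for the two primary scales only, but it shows what the team intends. A group-by-time model also contains a group term that equals the T1 arm difference when T1 is the reference. The model is usable, and only the choice of parameter needs naming.
- One of the three sources listed for document completion is an item of the ACP Engagement Survey, which is given at T0. The outcome's own row leaves T0 blank all the same.
- The documentation endpoint is a different case. Its measure is a review of a template that is an intervention component, and nothing says control GPs receive it. Template use is also summarised descriptively under *Process evaluation*. Without a measure in both arms there is no arm contrast to define.

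A reader might infer that the trial will report an effective intervention as ineffective on document completion. The article does not support that, because it would require applying the interaction mechanically to an endpoint it was not written for. A reader might also take document completion to be the main action outcome for patients. The article does not rank it so: it is one of several exploratory secondary outcomes, and appointing an SDM is another action outcome. The *Discussion* says that changes in behaviour-change states can indicate an ACP process even without such action outcomes in the short term.

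**Conclusion.** The point holds as an optional clarification for completion of new ACP documents. The endpoint has no T0 measurement, the one model effect parameter the article names cannot represent the intervention effect without one, and no other parameter is named for the GEE endpoints. If time by group were used, a sustained effect of any size would give an expected interaction of zero (assumed odds ratios of 6.0 and 6.0 give 1.0; in simulation, 5.2% rejection against 89.2% for the T1 contrast).

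The algebra needs no assumption beyond the T1/T2 schedule. The rejection rates rest on assumed completion rates and on 28 patients per arm without between-patient clustering, so they illustrate the mechanism and do not predict this trial's power. The primary analyses and the sample size are unaffected.

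**What to change.** Add to *Secondary efficacy analyses*, or confirm that the SAP already says: for endpoints without a T0 measurement, the intervention effect is the between-arm contrast at T1 and, separately, at T2; the time-by-group interaction is not the effect measure.

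For completion of new ACP documents, also adjust for the T0 item on earlier advance directives. It is already collected and is likely to be related to whether a new document is completed.

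Apply the rule to the documentation endpoint only if it can be measured in both arms.

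The cost is two sentences of analysis text. No new data, visits or participants are needed, and the same GEE model can be fitted with that one covariate added.
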